### Data Collection

On arrival at the ED, each patient undergoes a triage phase. A nurse is usually responsible for evaluating the severity of the health condition and the priority for clinical assessment (unless the patient enters the ED by ambulance under a red code). The nurse usually performs this task by collecting vital signs and recording the patient’s medical history. This information is then used to assign a color code representing the priority for further assessment. The patient then waits for the medical evaluation in a dedicated room where nurses can monitor the clinical condition of all attending patients. Participants who meet the inclusion criteria will be recruited during this phase and will be administered an electronic questionnaire (see Multimedia Appendix 1) about their smoking and nicotine product use habits and their medical history. This questionnaire serves to typify the patient’s use phenotype and quantify exposure to each product.

In addition to the questionnaire, medical data recorded at the triage phase, such as the NEWS, heart rate, blood pressure, blood oxygen saturation, respiratory rate, temperature, and fraction of inspired oxygen, will be collected.

After the assessment and management of each patient in the ED, the final diagnosis, final disposition, and color code at discharge or admission to a ward will be recorded (see Table 1). To avoid compromising the health of patients with severe disease requiring urgent medical attention, potential participants who arrive at the ED under a red code (ie, with a severe acute illness) will be asked to participate only after they are stabilized (ie, the questionnaire, NEWS, and vital signs will be recorded later).

Based on the responses to the questionnaire, participants will be divided in the following 5 smoking subgroups to facilitate analysis: (1) current tobacco smoker, (2) former tobacco smoker, (3) former tobacco smoker now using e-cigarettes and HTPs (exclusive use), (4) current tobacco smoker also using e-cigarettes and HTPs (dual use), and (5) never smokers or e-cigarette/HTP users.

After 1 month, data in the electronic case report form (eCRF) will be extracted for the statistical analysis.

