### Endpoint and Outcomes

The primary endpoint of the study is the association between the NEWS and product use phenotypes. Our hypothesis is that use of ENDS may be associated with a lower NEWS compared to cigarette smoking. If our hypothesis will be confirmed, the study will be replicated as a multicenter study to validate our findings.

Secondary outcomes will be hospital admissions (vs discharge) and length of stay in the ED and in the hospital (if admitted). Moreover, we will compare the prevalence of acute diseases known to be related to smoking between groups, specifically stroke, acute myocardial infarction, peripheral artery diseases, chronic obstructive pulmonary disease, asthma, and respiratory infections.

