### Statistical Analysis

Descriptive analysis will be performed by presenting numerical data as mean (SD) and categorical data as n (%). Patients will be classified according to product use as a current tobacco smoker, former tobacco smoker, former tobacco smoker now using e-cigarettes and HTPs (exclusive use), current tobacco smoker also using e-cigarettes and HTPs (dual use), and never smokers/never e-cigarette or HTP users.

Univariate comparisons will be performed using *χ*^2^ tests for categorical variables and the Kruskal-Wallis H test for the NEWS. Regression analyses will be performed to examine the association between the use of different types of products and the NEWS as well as secondary outcomes. Demographics, including age, sex (male or female), and educational level, as well as past medical history will be included as independent variables. Since the majority of ENDS users report current or past smoking, the smoking status of these users will also be recorded along with those who do not report any ENDS use. Therefore, the analysis will be adjusted for the smoking status of ENDS users. Additionally, secondary analyses will be performed for never-smoking ENDS users, if a sufficient number of such participants will be available. All analyses will be performed using SPSS v.25 (IBM) and a *P* value <.05 will be considered statistically significant.

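### The hypothesis that decides the multicentre study (ENDS users have a lower NEWS than cigarette smokers) is not targeted by any fixed contrast: the five-group test cannot answer it, and the planned regression leaves the comparison open

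*Protocol article*

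**What the plan says.** Under Endpoint and Outcomes, the protocol article sets a broad endpoint: "The primary endpoint of the study is the association between the NEWS and product use phenotypes". It then narrows to a directional statement about two products: "Our hypothesis is that use of ENDS may be associated with a lower NEWS compared to cigarette smoking". A decision follows: "If our hypothesis will be confirmed, the study will be replicated as a multicenter study to validate our findings".

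Under Data Collection, "participants will be divided in the following 5 smoking subgroups to facilitate analysis": current smokers, former smokers, former smokers now using e-cigarettes/HTPs (exclusive use), current smokers who also use them (dual use), and never users.

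Under Statistical Analysis, two analyses of the NEWS are planned. The first, listed among the univariate comparisons and so unadjusted, is "the Kruskal-Wallis H test for the NEWS". The second is a regression: "Regression analyses will be performed to examine the association between the use of different types of products and the NEWS as well as secondary outcomes". For the regression, age, sex and educational level "as well as past medical history will be included as independent variables", and the section adds that the analysis will be adjusted for the smoking status of ENDS users. Never-smoking ENDS users are assigned to a secondary analysis if there are enough of them. One significance threshold, P<.05, applies to everything; sidedness is not stated.

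**The concern.** The hypothesis concerns one difference, ENDS users against cigarette smokers. The Kruskal-Wallis test asks whether any of five groups differs from any other, without direction and without adjustment for age or history. Current smokers and never users make up most of the sample, so a gap between those two can produce significance whatever happens among ENDS users.

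The regression could isolate the right difference, but the article does not say which coefficient counts, whether dual users are ENDS users, smokers or both, or which of the two analyses decides. Five groups give 5 × 4 / 2 = 10 pairwise contrasts, all judged at P<.05.

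At stake is the meaning of confirmation. A significant five-group result driven by healthier never smokers could be reported as support for ENDS and used to justify expansion to the 10-12 EDs mentioned under Study Design.

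**Working it through.** **The plan's own figure.** The only sample figure is an accrual count. 70 patients per day × 28 or 29 days = 1960 or 2030, which agrees with the stated 2000 or so. The article gives no power, effect size or NEWS distribution, so there is no power statement to reproduce.

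**Group sizes at the enrolled N=901.** Rates from Study Population: current smoking 22.5%, former smoking 13.3%, ENDS use 5%, half of it dual. Assumption: these population rates hold in the ED, dual users are among the current smokers, and exclusive users are among the former smokers.
- Dual: 0.025 × 901 ≈ 23. Exclusive ENDS: 0.025 × 901 ≈ 23.
- Current smokers only: (0.225 − 0.025) × 901 ≈ 180.
- Former smokers without ENDS: (0.133 − 0.025) × 901 ≈ 97.
- Never: 901 − 180 − 97 − 23 − 23 = 578.

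Current smokers and never users are (180 + 578) / 901 = 84% of the sample.

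**Can the five-group test reject with no ENDS-smoker difference?** Assumed NEWS: negative binomial with dispersion parameter 0.6, capped at 17 (SD about 1.9 at mean 1.2 and 2.6 at mean 1.8). The direct contrast is a Mann-Whitney test of exclusive ENDS users against current smokers.

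| Means: smokers = exclusive = dual / former / never | Kruskal-Wallis P<.05 | Direct contrast P<.05 |
|---|---|---|
| 1.8 / 1.5 / 1.2 | about 62% | about 5% |
| 1.6 / 1.4 / 1.2 | about 34% | about 5% |

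A second assumed distribution (mean 2.0, SD 2.3), with only never users lower by 0.3 or 0.5 points, gives 27% or 71% at N=901 and 52% or 97% at N=2000. The direct contrast stays near 5%.

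**Free choice of ENDS group.** With exclusive users, dual users and smokers all equal, at least one of three comparisons with smokers (exclusive, dual, pooled) reaches two-sided P<.05 in about 11% of data sets. That counts either direction. If only results favouring ENDS count, the figure is about half, 5 to 6%, against 2.5% for one contrast fixed beforehand.

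**Does the smoking-status adjustment settle the regression?** Two ways to implement it:
1. *Five phenotype indicators plus current and former smoking indicators.* The current indicator is the sum of the current-smoker and dual columns; the former indicator is the sum of the former-smoker and exclusive columns. There are 7 columns of rank 5, so the added term carries no information, and the printed coefficients depend on which columns the software drops.
2. *An ENDS indicator plus smoking status.* Mean = b0 + bE·ENDS + bC·current + bF·former. Then exclusive − former = bE, and dual − current = bE. The hypothesised contrast, exclusive − current smokers, is bE + bF − bC. Take never 1.2, current 1.8, former 1.5, exclusive 1.5 and dual 1.8. Then b0 = 1.2, bC = 0.6, bF = 0.3 and bE = 0, while exclusive − current = 0 + 0.3 − 0.6 = −0.3. The ENDS coefficient is exactly zero although exclusive users score below smokers.

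**Power.** Let only exclusive users differ, by d standard deviations. For the five-group test, noncentrality = n·d²·(1 − n/N) on 4 df; at d = 0.5, 23 × 0.25 × (1 − 23/901) = 5.6, power 44%. For the direct contrast, z = 0.5 / √(1/180 + 1/23) = 2.26, power Φ(2.26 − 1.96) = 62%. At d = 0.3 the powers are 17% and 27%. At N=2000 and d = 0.5 they are 81% and 92%.

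**The case against.** The strongest reply is that Kruskal-Wallis is only the univariate step. The next sentence plans an adjusted regression of the NEWS on product type, which can yield an ENDS-versus-cigarette coefficient. This stands: a reader might infer that the five-group test is the only planned analysis, and the article does not support that.

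A reader might also infer that low power is a fault of Kruskal-Wallis in particular. It is not. The targeted contrast is also weak at N=901 because about 23 exclusive users are expected, and at N=2000 the five-group test does well for large effects. Nor are never-smoking ENDS users overlooked; they have their own secondary analysis.

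It can further be said that model family, reference group and ranking of contrasts belong in an analysis plan that is not shown, and that this is a pilot. Study Design ties expansion to successful completion rather than to the hypothesis. The sentence on smoking status may also mean no more than that the five groups already separate ENDS users by smoking history. These points lower the stakes. They do not remove the problem, because the article itself states the hypothesis, the consequence of confirming it, the tests and the threshold, and these do not meet. Under the mild reading of the adjustment, the contrast and the place of dual users are still open.

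The simulated means and spread are assumptions, and the direct contrast simulated is unadjusted, so it is not the planned regression.

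**Conclusion.** The concern holds in this form: the analyses listed do not target the directional hypothesis that triggers replication. The five-group test can reject with no ENDS-smoker difference, in about 34% to 62% of data sets at N=901 under the assumed skewed NEWS and gaps for never and former smokers, against 5% for the direct contrast. The regression could answer the question, but its deciding contrast is not fixed, and its smoking-status adjustment either adds nothing or moves the comparison to exclusive users versus former smokers and dual users versus current smokers. Open choice of the ENDS group roughly doubles the chance of a false finding, to about 11% in either direction.

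The percentages depend on the assumed distribution and on population use rates applying in the ED. The algebra on the regression and the mismatch between hypothesis and test do not.

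**What to change.** Before the data are analysed, add one paragraph that does the following.
- Names one primary contrast: exclusive ENDS users as the article defines them (former smokers now using e-cigarettes/HTPs) versus exclusive current smokers.
- Takes it from an ordinal (proportional-odds) regression of the NEWS on the five-level phenotype, adjusted for age, sex, education and past medical history, with no added smoking-status term. Test it two-sided at 5% and report the odds ratio with its 95% CI.
- States that this result alone decides whether the hypothesis is confirmed.
- Keeps Kruskal-Wallis as descriptive, and labels dual users versus smokers, ENDS users versus former smokers and all never-user contrasts as secondary.

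The cost is one paragraph; ordinal regression is available in the named software. The downside is that only one contrast can be called confirmatory, and its interval will be wide because the ENDS group is small. Naming the contrast does not cure that.

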## Methods

### Study Design

The Smoking or Nicotine Phenotype and Severity of Clinical Presentation at the Emergency Department (SMOPHED) study is an observational study with no intervention or randomization, analyzing the association between the patient’s health condition during an ED visit as well as the outcome (hospitalization and death) and different patterns of nicotine products use. Specifically, the study will explore relevant associations according to the smoking and ENDS product use status (current, former, and never use). The pilot phase of the study will take place at a single clinical center, aiming to evaluate its feasibility and analyze the results. Upon successful completion, there are plans to expand the study into a multicenter format involving a national network comprising 10-12 EDs.

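### Past smoking of ENDS users is handled only by a status that the five groups already fix, so residual confounding by smoking amount and recency may remain

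*Protocol article*

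**What the plan says.** The target is set in Endpoint and Outcomes: "The primary endpoint of the study is the association between the NEWS and product use phenotypes". The direction follows: "Our hypothesis is that use of ENDS may be associated with a lower NEWS compared to cigarette smoking". Replication in several centres is tied to that hypothesis being confirmed.

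Statistical Analysis gives the covariates: "Demographics, including age, sex (male or female), and educational level, as well as past medical history will be included as independent variables". It then notes that most ENDS users smoke or have smoked, and draws the consequence: "Therefore, the analysis will be adjusted for the smoking status of ENDS users". Study Design speaks of status in three levels: "according to the smoking and ENDS product use status (current, former, and never use".

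Data Collection sorts participants into five groups. Two of them involve ENDS, and both are defined partly by cigarette status. The exclusive-use group, for example, is the "former tobacco smoker now using e-cigarettes and HTPs (exclusive use" category, while dual users are current smokers. The same section says the questionnaire serves to type the participant's use and to "quantify exposure to each product". No section enters amount, duration or recency of smoking into a model. The limitations in the Discussion cover season, locality, self-report and recall, but not residual confounding by smoking history.

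**The concern.** The article recognises that ENDS users bring a smoking history with them, and it names a remedy. In the grouping it plans to use, that remedy does no work. Within each ever-smoker group, lifetime amount smoked can still vary. Among people who have stopped cigarettes, so can time since stopping. Either may differ between the groups being compared.

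This bears on the primary endpoint. If people who switched to ENDS smoked less over their lives than those who kept smoking, a lower NEWS could be credited to the product. If many switched because they had become ill, a real difference could be masked. The result is meant to inform the debate on harm reduction and to decide whether the study is replicated, so a reader will want to know whether smoking history was examined with the data collected.

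**Working it through.** **1. Group against status.**

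| Group | Cigarette status implied |
|---|---|
| 1 current smoker | current |
| 2 former smoker | former |
| 3 exclusive ENDS use | former |
| 4 dual use | current |
| 5 never smoker, never ENDS | never |

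**2. Redundancy.** Let D2 to D5 indicate groups 2 to 5, with group 1 as reference. Then former = D2 + D3 and never = D5. Both status indicators are sums of columns already in the model. The intercept and four group indicators make 5 columns of rank 5. Adding the two status indicators makes 7 columns, still of rank 5. The adjustment cannot change any group contrast.

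**3. If ENDS use is a separate term.** Smoking status then carries information, but it still treats light and heavy smokers, and recent and distant quitters, alike.

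**4. Size.** The article gives no effect size, SD or power for NEWS, so there is no figure of its own to reproduce. What follows is an illustration on assumed inputs. With no true ENDS effect, leaving out pack-years shifts the contrast by

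bias = slope per pack-year × difference in mean pack-years (exclusive ENDS users minus current-only smokers).

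| Assumed slope | Difference −10 | −5 | +5 |
|---|---|---|---|
| 0.01 | −0.10 | −0.05 | +0.05 |
| 0.02 | −0.20 | −0.10 | +0.10 |
| 0.03 | −0.30 | −0.15 | +0.15 |

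**5. Group sizes.** Study Population gives 22.5% current smokers, about 5% users of combustion-free products, and about half of these as dual users.
- N = 901 (enrolled): 901 × 0.05 × 0.5 = 22.5, about 23 exclusive users; 901 × 0.225 − 22.5 = 180 current-only smokers.
- N = 2000 (planned): 2000 × 0.05 × 0.5 = 50; 2000 × 0.225 − 50 = 400.

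**6. Precision, assuming a residual SD of 2.**
- N = 901: SE = 2 × √(1/23 + 1/180) = 0.44.
- N = 2000: SE = 2 × √(1/50 + 1/400) = 0.30.

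The largest shift in the table (0.30) is 0.68 SE and 1.0 SE respectively. At a two-sided 0.05 level this gives false-positive rates of about 10% and 17%.

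**7. Simulation.** Least squares, 2000 replicates per scenario, no true ENDS effect. Current smokers were assumed to average 20 pack-years (SD 12), with the slopes and differences above.

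| | Bias (NEWS points) | False positives, N = 901 | False positives, N = 2000 |
|---|---|---|---|
| Without pack-years | −0.30 to +0.15 | 5.0% to 9.0% | 4.7% to 17.5% |
| With pack-years | −0.013 to +0.011 | 4.0% to 6.1% | 4.1% to 5.7% |

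**8. Limits of the illustration.** It contains none of the planned covariates, so the gap in pack-years is crude. To the extent that age and medical history carry smoking dose, the remaining bias is smaller. It also treats the whole gap as confounding, whereas cigarettes smoked after others had switched are partly a consequence of not switching.

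**The case against.** The strongest defence is that this is a condensed article. Its covariate sentence is partly open-ended, nothing in it excludes exposure variables, and an analysis plan may exist that uses them. That carries some weight. But the article does commit to a covariate set and to a specific device for smoking history, and in the five-group model that device is empty. The point is about a stated choice, not an absent detail.

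Other objections stand and limit the claim:

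- Status is not the only control. Age absorbs part of lifetime smoking, and past medical history absorbs part of illness-driven switching. What is left is residual.
- The redundancy belongs to the five-group model. The article also speaks of regressing on types of product, and foresees a secondary analysis of never-smoking ENDS users, who fit none of the five groups. With ENDS use as its own term, status is informative.
- The questionnaire is in an appendix that is not shown. Quantified exposure need not mean that pack-years or a quit date were recorded, and 901 people have already been enrolled.
- At that size, with about 23 exclusive users on the article's prevalences, imprecision outweighs even the largest illustrative bias.
- Pack-years at the visit are partly downstream of switching. Adjusting for them without qualification could remove part of the effect under study.

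A reader might infer that the planned contrast is necessarily confounded, or that a lower NEWS in ENDS users would be spurious. The documents do not support this: they give no smoking amounts by group and no relation between smoking dose and NEWS.

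**Conclusion.** The point holds in a limited form. The stated adjustment for smoking status adds nothing to a model built on the five groups, and the exposure quantity that the questionnaire is said to collect has no stated role in the analysis. Residual confounding of the ENDS contrasts by amount and recency of past smoking may remain after adjustment for age, sex, education and past medical history.

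The gap in the stated model is clear from the text; the size of its effect is not. Direction and magnitude cannot be determined from the documents. The illustrative shifts of up to 0.30 NEWS points rest wholly on the assumed slope, pack-year gap and SD, and take no account of the planned covariates. They should not be read as an estimate for this study. The matter is worth settling before analysis, because a larger sample reduces random error but leaves this bias in place.

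**What to change.** In Statistical Analysis, as far as the questionnaire records the items:

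- **Ever smokers only:** add cumulative cigarette exposure (for example pack-years) to the regressions of NEWS and the secondary outcomes. Restricting the model to ever smokers avoids coding never smokers as zero and relying on linear extrapolation.
- **Exclusive ENDS users versus former smokers not using ENDS (group 3 versus 2):** also add years since stopping cigarettes. The term is undefined for current smokers and should be confined to this contrast.
- **ENDS users versus current smokers:** report results both with and without the cumulative-exposure term, and explain that smoking accrued after others switched lies partly on the causal path.

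In the Discussion, add residual confounding by smoking history to the limitations. If the questionnaire lacks these items, the limitation is what remains to be stated. Leaving out recent quitters or switchers can be an optional sensitivity analysis; the exclusive-use group is probably too small for it to be required.

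The cost is a few sentences and one or two model terms, and the Results section indicates that analysis awaits completion of the database. The downsides are the loss of some records with incomplete or poorly recalled smoking history, and slightly lower precision with few exclusive ENDS users.

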### Dissemination

The intention of the authors is to disseminate the results of the study through articles in high-quality, peer-reviewed journals and through conference abstracts.

## Results

In March 2024, we have enrolled a total of 901 participants (approximately 300 potential participants did not provide the informed consent to participate). The data will be analyzed by a statistician as soon as the database is completed. Full data will be published by December 2024.

